### Randomization and allocation

We will randomly allocate CR clinics (clusters) to one of the both study arms, stratified by the number of patients per month entering the CR program: small (up to 30 patients) versus large (30 patients or more). Allocation is based on randomization with variable block size (two or four), performed with dedicated computer software written in the statistical programming language R (version 2.13.1). To conceal allocation, the software is used to generate a list of unique codes for both strata, where each code corresponds to an allocation (study arm A or B).

Three researchers will be involved in the allocation procedure. When a clinic is willing to participate, the first researcher ([name]) will determine its stratum and communicate that to a second researcher ([name]) (without naming the clinic involved). The second researcher will look up the next unique code on the list for this stratum and pass that code to a third researcher who can determine the study arm, based on the given code. Using this procedure, both the second and third researchers are fully blinded for the allocation of clinics to the study arms during the procedure. The first researcher is not blinded but can however during this procedure not influence the allocation. Due to the characteristics of the intervention, it will not be possible to blind participants or the investigators providing the intervention.

### Statistical analysis

For the primary outcome measures, we will use mixed-effect logistic regression analysis [7,58], including clinic as random effect, to assess the effect of the intervention. Included covariates will be study arm, time since study start, and time × arm interaction. We will focus on the interaction term to assess the difference in change over the study period between the two arms—that is, the effect of the intervention—because we expect concordance to improve gradually.

For the secondary outcome measures, a similar analysis will be conducted, though replacing the logistic function by another link function as appropriate. Changes in practice variation will be assessed by including a random coefficient for ‘time since study start’ in the regression model and comparing the variation in estimated quality scores before and after the study.

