### Sample size

To calculate the minimally required number of CR clinics participating in the trial, data from a previous trial (concerning the effect of CDS on guideline concordance) was used [7]. Calculations were based on the normal approximation to the binomial distribution, using a type I error risk (alpha) of 5% and 80% power. Also, we assumed that participating clinics will see 350 CR patients, on average, during the study period of 1 year, and that there will be a design effect of 23.0 due to clustering. This is based on an intra-cluster correlation coefficient (ICC) of 0.063, which is the median ICC for process variables found in 21 studies, reported by Campbell et al. [57].

In the previous study [7], CDS increased concordance with guideline-recommended therapeutic decisions for exercise training from 84.7% to 92.6%. To demonstrate a further increase to 97.6% (+5%) in the current study, at least 19 participating clinics (6,712 patients) are required under the assumptions given. For education, the concordance level previously rose from 63.9% to 87.6%. Demonstrating a further increase to 95.1% (+7.5%) requires 14 participating clinics (5,057 patients). For relaxation therapy, the previous study showed an increase from 34.1% to 59.6%, and showing an additional increase to 74.6% (+15%) requires ten participating clinics (3,517 patients). For lifestyle change therapy, finally, no significant effect of CDS was observed in the previous study (57.4% vs. 54.1%). To prove that the current intervention causes an increase from 57.4% to 72.4% (+15%) will also require that 13 clinics (3,632 patients) participate. Based on these results, we aim to include at least 19 CR clinics in our study.

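### The primary time × arm test appears to use a clinic random intercept only, so its type I error exceeds 5% if clinics' time trends differ

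*Protocol article*

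**What the plan says.** The Statistical analysis section of the protocol article sets out the primary model in two sentences. The random part is given as: "we will use mixed-effect logistic regression analysis [7,58], including clinic as random effect, to assess the effect of the intervention". The fixed part is arm, time since study start and their interaction. The interaction is the treatment effect: "We will focus on the interaction term to assess the difference in change over the study period between the two arms".

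A random coefficient for time appears once, in the following paragraph on secondary outcomes: "Changes in practice variation will be assessed by including a random coefficient for" time since the start of the study. No such term is named for the primary outcome. The article mentions no cluster-robust, permutation or cluster-level alternative.

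The Sample size section plans the trial "using a type I error risk (alpha) of 5% and 80% power". It states that "there will be a design effect of 23.0 due to clustering", and adds: "This is based on an intra-cluster correlation coefficient (ICC) of 0.063". That ICC concerns differences between clinics in level. The section says nothing on how far clinics' time trends differ.

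**The concern.** Clinics are randomised, and the quantity tested is a difference between arms in change over the year. The replicates for that comparison are the clinics' trends. A random intercept absorbs differences in clinics' starting level. For the slope comparison it then treats the patients within a clinic as independent, as if every clinic in an arm shared one underlying trend. If clinics drift at different rates for reasons unrelated to arm, the model has no term for that drift and part of it can be attributed to the intervention.

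What is at stake is the confirmatory test of the trial's key question, with about 18 or 19 clusters. A standard error that is too small gives confidence intervals that are too narrow and a false-positive rate above the one planned.

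**Working it through.** **1. The plan's own figures.** Design effect: 1 + (350 − 1) × 0.063 = 22.987, which matches the stated 23.0. Exercise training, 92.6% to 97.6%, two-sided 5%, 80% power, pooled variance under the null:

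n = [1.96 × √(2 × 0.951 × 0.049) + 0.8416 × √(0.926 × 0.074 + 0.976 × 0.024)]² / 0.05² = 291.4, rounded up to 292.

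292 × 22.987 = 6,712, the figure in "To demonstrate a further increase to 97.6% (+5%) in the current study, at least 19 participating clinics (6,712 patients) are required". The 5% is therefore two-sided. (292 is a per-arm number, which is a separate matter from this point.) The calculation compares two proportions with clustering in level. It contains no slope and no slope variance.

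**2. Inputs for the type I error.**
- Patients per clinic: 350 over one year (Sample size section). Even accrual is assumed, so time in years has variance 1/12.
- Baseline concordance p: 92.6% (exercise training) and 59.6% (relaxation), from the same section.
- τ, the between-clinic SD of the time slope in log-odds per year. The article does not give it, so it is an assumption shown over a range.

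**3. Formula.** With clinic level removed, the sampling variance of one clinic's slope is v = 12 / [350 p(1 − p)].
- p = 0.926: p(1 − p) = 0.0685, v = 0.500.
- p = 0.596: p(1 − p) = 0.2408, v = 0.142.

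The intercept-only model uses v, whereas the true variance of a clinic's slope is v + τ². Both are averaged over the same clinics, so the number of clinics cancels from the ratio:

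type I error = 2 × [1 − Φ(1.96 / √(1 + τ²/v))].

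Example, p = 0.596, τ = 0.3: 1 + 0.09/0.142 = 1.632; √1.632 = 1.278; 1.96/1.278 = 1.534; error = 12.5%.

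**4. Results, nominal 5%.** The simulation used 18 clinics with 12 months of 29 patients each, no intervention effect, a maximum-likelihood logistic mixed model, a Wald test and 600 runs per cell. The Monte Carlo standard error is about 0.9 points near 5%. The intercept SD was 0.9 at 92.6% and 0.51 at 59.6%.

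| τ | 92.6% analytic | 92.6% simulated | 59.6% analytic | 59.6% simulated |
|---|---|---|---|---|
| 0 | 5.0% | 6.5% | 5.0% | 3.0% |
| 0.1 | 5.2% | not run | 5.8% | not run |
| 0.2 | 5.9% | 7.5% | 8.3% | 7.7% |
| 0.3 | 7.1% | 7.8% | 12.5% | 13.2% |
| 0.5 | 10.9% | 12.3% | 23.8% | 21.3% |

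For scale: at p = 0.596, τ = 0.3 means that clinics one SD apart in trend separate by about 0.3 × 0.241 = 7 percentage points over the year.

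**5. With a clinic random slope added (same simulation, τ from 0.2 to 0.5).**
- Wald z: 5.2-6.5% at 92.6% and 6.2-8.5% at 59.6%.
- t on 16 df: 3.7-5.5% and 4.8-5.8%.

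At τ = 1.0 some excess remained even with t on 16 df (7.8% and 11.5%). This may partly reflect the small number of clinics and the numerical integration used.

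**6. Power with the slope variance counted.** This is an approximation: 9 clinics per arm, t on 16 df, and the planned effect reached linearly by year end. The standard error is √[(v₀ + τ²)/9 + (v₁ + τ²)/9]. Here v₀ is taken at the baseline proportion and v₁ at the midpoint of the planned rise.
- Relaxation: effect = logit(0.746) − logit(0.596) = 0.689; v₀ = 0.142, v₁ = 0.155. Power is 94%, 85% and 58% at τ = 0, 0.25 and 0.5.
- Exercise training: effect = logit(0.976) − logit(0.926) = 1.179; v₀ = 0.500, v₁ = 0.736. Power is 85%, 81% and 71%.

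**The case against.** **The text does not literally exclude a random slope.** A condensed article may leave details of the random-effects structure to an analysis plan. That much stands, and degrees of freedom alone would not be a finding. But the section describes the random part of the primary model and names a random time coefficient only for another analysis. Intercept-only is therefore the natural reading, and at the least the text needs clarifying.

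**The size is assumed.** This stands. At τ = 0.1 the excess is trivial. At 59.6%, τ = 0.5 is a strong assumption: one year's drift would then about equal the whole between-clinic spread in level implied by the ICC, √(0.063/0.2408) = 0.51 on the logit scale.

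A reader might draw three stronger conclusions that the article does not support:
- *That the planned design effect of 23 is wrongly lost from the test.* It describes variation in clinic level, which properly cancels from a within-clinic time contrast. With τ = 0 the analytic error is exactly 5%. Only slope variation is unaccounted for.
- *That the plan itself expects clinics' trends to differ.* It adds a random time coefficient to assess whether variation on the quality indicators changes. Estimating a quantity is not predicting that it is large. The freedom of each team to choose its own actions is mainly a source of differing response to the intervention, which is absent if the intervention does nothing anywhere.
- *That the false-positive rate is above 5% without condition.* It is above 5% only if slope variance is above zero.

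**Conclusion.** The point holds in conditional form. On its natural reading, the primary model lacks the error term that a cluster-randomised comparison of trends needs. The direction follows from algebra for any τ above zero. The magnitude rests on a τ that the article does not supply: about 5.2-5.8% at 0.1, 6-8% at 0.2, 7-12.5% at 0.3 and 11-24% at 0.5, the lower end for 92.6% baseline concordance and the higher for 59.6%. These figures also assume 350 patients per clinic accruing evenly. The excess may be negligible or substantial, and an intercept-only analysis would not show which.

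**What to change.** State that the primary model includes a clinic random slope for time, correlated with the clinic random intercept. Do the same for the patient-level secondary models that test time × arm; the structure indicators are clinic-level yes/no items and need separate handling. Refer the interaction to a t distribution on about (clinics − 2) degrees of freedom, or to a permutation test over clinics within the two size strata. Keep the intercept-only model as a sensitivity analysis.

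The text change is short, but it has a price. If trends differ, confidence intervals widen and power falls, in the approximation above from 94% to 58% for relaxation as τ goes from 0 to 0.5. The two-proportion calculation in the Sample size section does not cover this, so the power of the slope test should be given over a range of slope SDs. If slope variation is very large, t-based inference may still exceed 5%, and the permutation test is then preferable.

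### The clinic-size strata overlap at 30 patients per month, and the size stratum used for allocation is left out of the listed model covariates

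*Protocol article*

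**What the plan says.** **Allocation (Protocol article, Randomization and allocation).** Clinics are randomised "stratified by the number of patients per month entering the CR program: small (up to 30 patients) versus large (30 patients or more"). The codes are generated in short blocks whose size varies between two and four. The first researcher determines the clinic's stratum and passes it on without naming the clinic. "The second researcher will look up the next unique code on the list for this stratum", and a third researcher translates the code into an arm. Of the first researcher the article says: "The first researcher is not blinded but can however during this procedure not influence the allocation".

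**Analysis (Protocol article, Statistical analysis).** The primary analysis is a mixed-effect logistic regression "including clinic as random effect". The fixed effects are then listed: "Included covariates will be study arm, time since study start, and time × arm interaction". The estimand is the interaction: "We will focus on the interaction term to assess the difference in change over the study period between the two arms". The same structure carries over to the other outcomes: "For the secondary outcome measures, a similar analysis will be conducted", with another link function where needed. A random coefficient for time is mentioned only for the assessment of practice variation. Clinic size does not appear in the analysis section.

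**The concern.** There are two linked points.

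1. **The strata are not disjoint.** Both categories contain the value 30, and the article gives no rule for a clinic at that value. The stratum decides which code list supplies the next allocation. A clinic that fits both lists therefore leaves a choice to the one person in the procedure who is not blinded. The article's assurance about that person holds only if stratum membership is fixed by an objective rule.

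2. **The model does not follow the design.** Size was thought important enough to balance on, yet the listed fixed effects are arm, time and their interaction. This is a stated covariate list, not silence that a later analysis plan would fill. Analysing by the groups within which clinics were randomised is the usual consequence of stratifying. Because the tested effect is a difference in trend, the term that matters is stratum × time. With 18 clinics in the Abstract, about nine per arm, any clinic-level variation in trend that size explains would be worth removing.

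**Working it through.** The plan gives no figure of its own for this point, so there is none to reproduce. The check is a reading of the two sections plus four short calculations.

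**1. Is a clinic at the cut-off realistic?** The Sample size section assumes 350 patients per clinic per year: 350/12 = 29.2 per month, next to 30. If a single month's count at such a clinic were Poisson with mean 29.2 (assumption), the chance of exactly 30 would be about 7.2%. This shows that the case is not remote. It does not show that any clinic sits there.

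**2. Can the choice of list matter?** Assume that blocks of two and four are equally likely and that earlier allocations are known.
- One allocation into a new block, the next is the opposite arm with probability 1 (block of two) or 2/3 (block of four): ½ × 1 + ½ × 2/3 = 5/6. Whatever the mix of block sizes, the value lies between 2/3 and 1.
- Two equal allocations at the start of a block imply a block of four, so the next two are certain.

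When the two lists lean towards different arms, choosing the list for a borderline clinic is close to choosing its arm.

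**3. What does the omission do when trends are analysed by clinic?** Illustrative simulation with assumed inputs:
- 18 clinics: 10 small with 246 patients and 8 large with 480, arms balanced within strata.
- Between-clinic SD 0.47 logit, baseline concordance 59.6%, no true arm effect.
- A straight-line slope per clinic, then ordinary least squares on the slopes; 2,000 runs, Monte Carlo standard error about √(0.05 × 0.95/2000) = 0.5 percentage points.

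| Assumed effect of size | Rejection without stratum | With stratum |
|---|---|---|
| None | 5.65% | 5.55% |
| Level only, 0.5 logit | 5.55% | 5.50% |
| Level, plus trend 0.5 logit/year | 2.05% | 4.60% |
| Level, plus trend 1.0 logit/year | 0.20% | 4.10% |

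In this slope analysis the stratum term plays the part of stratum × time. The test is not inflated. It becomes conservative when size shifts the trend and the analysis ignores it.

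**4. And under a random intercept only?** This uses a linear approximation, not the logistic model, with the same clinic sizes, ICC 0.063 and entry spread evenly over the year. Letting size explain 10% or 30% of between-clinic level variance, and adding size and size × time, changes the standard error of time × arm by less than 0.01%. I also simulated a within-clinic linear model with trend shifts of 0.5 and 1.0 logit/year. Rejection without versus with stratum × time was 5.40% versus 5.45% and 5.00% versus 5.20%, so no material difference. The gain therefore depends on clinic-level variation in trend entering the standard error.

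**The case against.** **On the cut-off.** The wording can be read as a slip for below 30 versus 30 and above, and it affects only a clinic at 30. The second researcher holds the list and does not know which clinic is concerned, and the third decodes it, so choosing a list is not choosing an arm unless the next allocation can be predicted. This limits the reach of the point but does not remove it. The overlap is in the text, short blocks make some allocations predictable to someone who knows the earlier ones, and that person assigns the stratum. A reader might infer that allocation was manipulated; nothing in the article supports that.

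**On the model.** The clinic random effect absorbs size-related differences in level, and time × arm is estimated from change within clinics, so a size main effect does almost nothing for it. The primary model as stated has no random slope, and the article gives no evidence that size affects the trend. All of this stands, and it keeps the expected gain modest. Three stronger readings should be resisted:
- That the stratification goes unused. It is used in the allocation; only the analysis leaves it out.
- That the omission costs a definite share of the standard error. Any such percentage needs an assumed proportion of trend variation explained by size, and a random slope that the primary model does not state.
- That the omission makes the test too liberal. The calculations show no such inflation.

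**Conclusion.** The point holds in two parts of different weight.

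- **Overlapping strata: wrong as written.** A clinic at 30 patients per month fits both lists, and its classification falls to the unblinded first researcher. The weakness is confined to clinics at the cut-off. It becomes an influence on allocation only if that researcher can anticipate the next codes, which short blocks make possible.
- **Stratum missing from the model: a cheap improvement.** The stated covariates do not reflect the stratified design, and the secondary analyses inherit this. The gain is modest. It is negligible if size affects level only or if the primary model keeps a random intercept alone, and it is real mainly if size is related to the time trend and clinic-level trend variation is reflected in the standard error. The size of such a relation is an assumption; the article gives none.

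Neither part changes the stated sample size, alpha or power.

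**What to change.** 1. In Randomization and allocation, make the strata disjoint: fewer than 30 versus 30 or more patients per month, counted over a stated period before enrolment, so that the first researcher applies a rule rather than a judgement.
2. In Statistical analysis, add size stratum and, because the tested effect is time × arm, stratum × time as fixed effects in the primary and secondary models.

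The first change costs only wording. The second costs one or two of about 16 clinic-level degrees of freedom (18 clinics less two arm means). If clinics were already enrolled under the present wording, report how any clinic at exactly 30 was classified.

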## Methods

### Study design

The effect of the intervention will be evaluated in a multicenter cluster-randomized study with a balanced (2 × 2) incomplete block design. Cluster-randomization is chosen to avoid contamination among professionals within the same clinic [25]. During the trial, clinics will be divided into two study arms (A and B). Using the multidisciplinary character of CR treatment, each arm will receive the intervention (a web-based QI system with feedback and educational outreach visits) directed at one out of the two domains described in the CR guidelines [26]. Clinics allocated in arm A will receive the intervention directed at improving guideline concordance for the psychosocial domain, clinics in arm B for the physical domain (see Figure 2 for an overview of the study flow). In this way, both study arms will serve as each other’s control. For all participating clinics, the study period is 1 year.

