### Outcome measures

As in most guideline implementation studies, the proposed intervention is targeted at health care providers and is therefore expected to have a direct effect on process outcomes and to have only indirect, long-term effects on patient outcomes. The primary outcome measure will therefore be concordance, at patient level, to national CR guidelines with respect to the needs assessment (concordance of clinical decisions with the guidelines, for four group-based therapies). We will measure whether patients are treated according to the recommendations of the guidelines (i.e., treating patients who should have been treated and not treating patients who should have been untreated).

Secondary outcome measures are changes in performance of participating clinics as measured by 18 quality indicators for CR (see Table 3) and changes in practice variation on these indicators. Table 1 describes how the indicator set was developed [24].

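### The protocol is inconsistent on one versus several primary outcomes: time × arm measures the intervention only within a single therapy, and testing per therapy gives four primary tests, each at 5%

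*Protocol article*

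**What the plan says.** - **Design.** Study design states that "each arm will receive the intervention (a web-based QI system with feedback and educational outreach visits) directed at one out of the two domains". Tables 2 and 3 assign education and lifestyle change to arm A, and exercise and relaxation to arm B. Each arm is the control for the other arm's therapies.
- **Outcome, singular.** Outcome measures: "The primary outcome measure will therefore be concordance, at patient level", with the addition "concordance of clinical decisions with the guidelines, for four group-based therapies". The abstract and Aim and objective also name one primary outcome.
- **Outcome, plural.** Statistical analysis: "For the primary outcome measures, we will use mixed-effect logistic regression analysis".
- **Model.** "Included covariates will be study arm, time since study start", and the interaction of the two, with clinic as a random effect. The interaction is used "to assess the difference in change over the study period between the two arms", and that difference is called the effect of the intervention.
- **Sample size.** One alpha of 5% and 80% power are stated. Four calculations follow, one per therapy, and the largest sets the target of 19 clinics.

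The protocol does not say whether the model is fitted once or per therapy. The covariate list has no therapy, domain or targeted term.

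**The concern.** Treatment in this design is a property of the arm and the therapy together. A model that knows only the arm identifies the intervention effect if it is fitted to one therapy at a time. If it is fitted to an outcome that combines the four therapies, both arms are expected to improve, each on its own two, and the between-arm difference in change says almost nothing about whether the intervention works.

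If it is fitted per therapy, the contrast is sound, but one question about effectiveness is answered by four tests, each sized at the full 5%. Which pattern of results would support the intervention is then open. Each clinic also supplies targeted and untargeted therapies, and four separate fits do not use that comparison.

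**Working it through.** **1. Inputs.** Planned levels come from Sample size, target arms from Tables 2 and 3. The log-odds change is ln[p₂/(1−p₂)] − ln[p₁/(1−p₁)].

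| Therapy | Targeted in | From | To | Gain (points) | Log-odds change |
|---|---|---|---|---|---|
| Exercise | B | 92.6% | 97.6% | 5.0 | 1.18 |
| Education | A | 87.6% | 95.1% | 7.5 | 1.01 |
| Relaxation | B | 59.6% | 74.6% | 15.0 | 0.69 |
| Lifestyle | A | 57.4% | 72.4% | 15.0 | 0.67 |

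**2. The plan's own figures.** The design effect is 1 + 349 × 0.063 = 22.987. The two-proportion formula is n = [1.96·√(2p̄(1−p̄)) + 0.84·√(p₁(1−p₁) + p₂(1−p₂))]² / (p₂−p₁)². In table order it gives 292, 220, 153 and 158 per arm. Multiplied by 22.987 these are 6,712, 5,057, 3,517 and 3,632, which match all four stated patient numbers. Each therapy was therefore sized at an undivided two-sided 5%. (The match holds only if the stated numbers are per arm, which is a separate matter.)

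**3. Pooled reading.** Take the unweighted mean concordance over four therapies.
- Start, both arms: (92.6 + 87.6 + 59.6 + 57.4)/4 = 74.3%.
- End, arm A: (92.6 + 95.1 + 59.6 + 72.4)/4 = 79.9%, a gain of (7.5 + 15)/4 = 5.6 points.
- End, arm B: (97.6 + 87.6 + 74.6 + 57.4)/4 = 79.3%, a gain of (5 + 15)/4 = 5.0 points.
- Difference between arms: 0.6 point. Mean effect on a targeted therapy: (5 + 7.5 + 15 + 15)/4 = 10.6 points.

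On the log-odds scale the pooled arm difference is ln(0.79925/0.20075) − ln(0.793/0.207) = 0.04. A simulation with 18 clinics (the abstract's number), 350 patients each, ICC 0.063 and 200 runs gave 0.02 (SD 0.10) for pooled time × arm and 0.77 (SD 0.19) for targeted × time. It used fixed clinic effects in place of the random intercept and equal patient numbers per therapy. A composite of all four decisions concordant also nearly cancels: if the therapies are independent it moves from 27.8% to 38.0% in A and 36.6% in B.

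**4. Per-therapy reading.** With arm A coded 1, the same simulation gave time × arm of −1.23 (exercise), +0.99 (education), −0.71 (relaxation) and +0.66 (lifestyle). These recover the planned sizes, with the sign reversed for the two arm-B therapies.

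**5. Four tests at 5%.** If independent, the chance of at least one false positive is 1 − 0.95⁴ = 18.5%. It can lie between 5% (fully dependent) and 4 × 5% = 20%. A simulation with clinic-specific time slopes gave about 18–20%. It assumed a correlation of 0.5–0.9 between a clinic's levels at months 0 and 12, and half of the slope variance shared across therapies. Neither value is in the protocol.

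**6. Power under the same assumptions.** Ranges cover the assumed correlations and repeated runs.

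| Effects | Each therapy alone at 5% | One targeted × time test at 5% |
|---|---|---|
| As planned | 59–92% | near 100% |
| Half the planned size | 16–39% | 69–90% |

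The single test held its error rate at about 5%.

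**The case against.** The strongest defence is that the plan already means a per-therapy analysis. The plural in Statistical analysis, the mention of four therapies in Outcome measures, the four separate sample sizes and the statement that the arms control each other all point that way. Within a therapy, arm is the intervention indicator up to sign. This stands. A reader might infer that the primary model cannot detect a working intervention, or that arm is simply the wrong variable. The protocol does not support either: cancellation needs a pooled fit, which the singular wording allows but no section states.

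Two further inferences also fail. One is that the block design was chosen for its within-clinic contrast; Strengths and limitations gives clinic motivation as the reason. The other is that power per therapy is low as planned; the 16–39% range applies only at half the planned effects, a scenario the plan does not contain.

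It is also fair that a success rule is often left to the analysis plan, which is not shown, and that requiring all four therapies to succeed would not inflate the error. That limits the multiplicity point. It does not remove what the protocol itself prints: singular against plural outcomes, the unqualified equation of the arm difference with the intervention effect, and four sizings under one 5%.

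Finally, a stacked model changes the primary estimand from four effects to one average. That is true and has to be accepted knowingly.

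**Conclusion.** The point holds as a contradiction to be resolved, not as proof that the primary analysis fails. The protocol names one primary outcome in three sections, several in another, and sizes four. Its time × arm term is the intervention effect only therapy by therapy.

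On a pooled outcome it would see 0.6 point where the planned mean effect is 10.6. On the better-supported per-therapy reading the estimates are valid. The chance of at least one false positive is then about 18–20%, provided that any single success counts, and the within-clinic contrast goes unused. The power comparison rests on the assumed slope variation. The cancellation is arithmetic on the plan's own targets, with the therapies weighted equally. The change should be made before the data are analysed.

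**What to change.** - State whether there is one primary outcome or four, use the same wording in every section, and state that arm × time is never fitted to an outcome pooled over therapies.
- Make one targeted × time test at 5% the primary analysis, on one record per patient and therapy. Code targeted as 1 when the therapy belongs to the clinic's arm. Include therapy, time, therapy × time, targeted and targeted × time.
- Include random intercepts and time slopes for clinic and for clinic by therapy, with a stated simplification if the model does not converge (18 or 19 clinics is few for this structure). Allow for repeated records from the same patient.
- Report the four therapy-specific effects beside the primary estimate, with Holm adjustment.
- Define how physical activity is assigned. Tables 2 and 3 exclude it from arm A's lifestyle therapy and place it with exercise in arm B, so a 0/1 code for lifestyle needs a rule.

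Alternatively, keep four per-therapy tests with Holm adjustment and state the success rule.

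**Cost.** No change to conduct or data collection. The primary estimate becomes an average over therapies whose planned effects differ (about 0.67 to 1.18 log-odds), so it must be read beside the separate effects. The Holm-only alternative keeps the four estimands but costs power. At its strictest step (0.05/4 = 0.0125) the unclustered numbers per arm rise from 292, 220, 153 and 158 to 415, 312, 218 and 225, about 42% more (415/292 = 1.42).
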